| Statistical methods & analyses | 
An interim analyses applying the Haybittle Peto rule for early stopping had been applied. Safety and efficacy have been analyzed on day 30 after n=200 patients had been randomized. level of neutralizing antibodies (primary endpoint) had been significantly lower in the homologous Vaxzevria arm compared to the heterologous (p-value < 0.001) this arm had been stopped. Already recruited participants in all arms will be further followed for durability of antibody response and the number of breakthrough infections. New participants in the two remaining arms are recruited with the aim to recruit up to 1000 participants in each of these two arms to analyse the number of breakthrough infections. Efficacy analysis will employ contingency table analysis,
                                                                                                                                                                                                                                                                   |

|  |                                                                                                          |
|--|----------------------------------------------------------------------------------------------------------|
|  | chi-square testing and a logistic regression adjusting for the stratifying variables study site and sex. |
|--|----------------------------------------------------------------------------------------------------------|

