First reports from Israel indicate that durability of vaccine protection after two Comirnaty doses might be limited. We therefore plan to compare the level and durability of cross-neutralizing antibodies induced by classical BNT162b2 and ChAdOx1-S vaccinations with the heterologous prime and boost with ChAdOx1-S followed by BNT162b2, respectively.

While analyzing neutralizing antibody responses on day 30 in the participants that had already been recruited for our study we observed a number of participants with no or only

very low titers of neutralizing antibodies against non-immune escape virus variants. The number of non-responders was even higher for immune escape virus variants such as B.1.351. These non-responders were mainly found in the homologous Vaxzevria group (2 against all three analyzed virus variants (B.1.1.7, B.1.351 and B.1.617.2), further 3 against B.1.351 and B.1.617.2 and additional 14 only against B.1.351). Only one person in the heterologous group did not develop neutralizing antibodies against B.1.617.2 but high titers of neutralizing antibodies against the other two variants. The “Nationales Impfgremium” in Austria recently recommended a third vaccination for non-responders of a complete vaccination scheme starting 4 weeks after the second immunization. Therefore, we plan to apply a third dose with Comirnaty in participants that do not have neutralizing antibodies against the wild-type variant on day 90, which will be applied between day 110 and 180.

The “Nationales Impfgremium” in Austria recommends a third vaccination in fully vaccinated persons either 6-9 or 9-12 months after completion of the regular vaccine scheme depending on risk factors and the type of vaccine used for the basic immunization. We therefore plan to offer all participants that received the second vaccination during this study and were followed until day 180 a third dose with Comirnaty. This third dose will especially be recommended for participants with no or low levels ( $<1:64$ ) of cross-neutralizing antibodies against B.1.351. We will analyze immune responses, especially cross-neutralizing antibodies after the third dose.

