## 4.1 Number of Patients

A total of 2124 subjects will be included in this study. Each arm of 1000 subjects will be vaccinated as it follows:

Group A: ChAdOx1-S prime and BNT162b2 boost

Group B: BNT162b2 boost prime and BNT162b2 boost

Group C: ChAdOx1-S prime and ChAdOx1-S boost (this arm has been closed after 124 subjects have been randomized to; therefore, the total number of subjects is reduced from 3000 to 2124).

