## 11. Statistics

### 11.1 Sample Size

The sample size is generated for the primary endpoint of a superiority testing of level of neutralizing antibodies against the B.1.351 variant between the two randomized study arms (arm 1: ChAdOx1-S prime & boost, arm 2: ChAdOx1-S prime and BNT162b2 boost). A comparison against arm 3 (BNT162b2 prime & boost) is exploratory and will be done descriptively.

In a study of Madhi  92% of participants showed neutralizing antibodies following vaccination with ChAdOx1-S prime & boost against the B.1.1.7 (British) variant and 58% against the B.1.351 (South African) variant. Focusing on the improvement of the heterologous vaccination with the Biontech boost against the South African variant with regard to primary the endpoint of neutralizing antibodies we consider a sample size of n=1000 per study arm as appropriate. With this sample size, we can detect an increase in the percentage of participants with neutralizing antibodies against the South African variant from 58% to 65.5% as statistically significant, with a power of >90% and alpha of 5%. If the increase is 10% the statistical power would be >99%.

For the secondary endpoint of efficacy against breakthrough infection with the B.1.351 variant, based on the current number of 8 new cases per week in Tyrol with the B.1.351 variant we expect 208 cases during the next 180 days with no change in rate of infection.

Currently, the B.1.351 is concentrated in 4 districts – Kufstein, Schwaz, Innsbruck Land and Innsbruck Stadt giving a total population of 416,758, this gives a rate of 49,9/100,000 people in 180 days. As not all cases are sequenced we estimate that only 5% of B.1.351 variants are detected, this would mean in total a rate of approximately 1000 cases per 100000 population of the B.1.351 variant would occur over 180 days – this means 10 cases per 1000. This scenario could lead to 10 cases in the ChAdOx1-S prime & boost arm (Arm 1) and 0 case in the ChAdOx1-S prime and BNT162b2 boost arm (Arm 2). In the extreme situation that all 10 cases occur in Arm 1, this would be statistically significant. However, due to the decreasing infection rates in Tyrol we would currently consider this an underpowered analysis and as such would perform a posthoc power analysis. In addition, a second immune escape variant, B.1.1.7.+E484K has recently occurred in Tyrol with over 900 cases until now. However, the development of this outbreak is currently not predictable.

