### 11.3.5 Data Analysis

#### Efficacy analysis

Efficacy analyses are performed for the comparison of neutralizing titers against the wild type and escape variants at 30 days (primary endpoints of the study) and on breakthrough

infections of wild type/ escape variants (secondary endpoint) at 180 days. The main efficacy analysis is performed between the two randomized arms (Arm C: ChAdOx1-S prime & boost; Arm A: ChAdOx1-S prime and BNT162b2 boost).

Neutralising titer and breakthrough infection are both defined as binary quantitative variables.

Hypothesis testing between the two treatment arms will be performed using Chi testing and logistic regression including stratification variables.

Efficacy analyses will be performed on the ITT and PP populations. The analysis of the ITT population will be considered as the primary analysis. All statistical tests are two-sided with a significance level of 0.05.

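### The planned ordinary logistic regression has no finite arm effect on the protocol's own zero-event counts, and its Wald p-value then contradicts the chi-square test named beside it

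*Protocol*

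**What the plan says.** Section 11.3.5 makes both efficacy endpoints binary: "Neutralising titer and breakthrough infection are both defined as binary quantitative variables". For the tests it says "Hypothesis testing between the two treatment arms will be performed using" chi-square "testing and logistic regression including stratification variables". The Synopsis agrees, naming contingency tables, "chi-square testing and a logistic regression adjusting for the stratifying variables study site and sex". On level: "All statistical tests are two-sided with a significance level of 0.05". Neither place names a Wald, likelihood-ratio, exact or penalised version of the model, or says which of the two analyses decides.

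The counts come from three other places:

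- Section 1.3 gives interim denominators of 100 (homologous Vaxzevria) and 106 (heterologous). In the homologous group 2 participants lacked antibodies to all three variants, 3 more to B.1.351 and B.1.617.2, and 14 more to B.1.351 only. In the other group, "Only one person in the heterologous group did not develop neutralizing antibodies against B.1.617.2", and that person had high titres against the other two variants.
- Section 11.1 forecasts 10 breakthrough cases in the homologous arm and none in the heterologous arm, at 1000 each: "In the extreme situation that all 10 cases occur in Arm 1, this would be statistically significant".
- Section 4.1 says of Group C that "this arm has been closed after 124 subjects have been randomized to" it, while Group A may still grow to 1000.

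**The concern.** When one arm has no events, the likelihood keeps rising as the arm coefficient goes to infinity. Software then prints an arbitrary large coefficient, a huge standard error and a Wald p-value close to 1. Adding site and sex cannot help, because the empty arm stays empty within every stratum. The adjusted analysis named in the plan would therefore give no usable effect estimate for B.1.351, the variant on which the trial was sized, or for the breakthrough scenario that section 11.1 calls significant. Two analyses named in one sentence would give opposite answers, with no rule for choosing between them.

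The second issue is narrower. Group C is fixed at 124 while Group A can grow. If those two are compared on a rare event, the expected counts become very small, and the chi-square approximation may call a single infection significant.

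**Working it through.** **Inputs.** Homologous non-responders: B.1.1.7 2; B.1.617.2 2+3=5; B.1.351 2+3+14=19; all of 100. Heterologous: 0, 1 and 0 of 106. Forecast: 10/1000 v 0/1000. Two-sided 5% level.

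**The plan's own figures.** Power for 58% v 65.5% at 1000 per arm comes to 93.3%, and for 58% v 68% to 99.6%, so the stated >90% and >99% reproduce. At the planning rates (420 v 345 non-responders per 1000) every method gives p of about 0.0006. The claim that 10 v 0 is significant also reproduces, as shown next.

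**Chi-square.** With events a and c, arm sizes n1 and n2, m=a+c and N=n1+n2, the statistic is N·(a·(n2−c) − c·(n1−a))² / (n1·n2·m·(N−m)).

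- 10 v 0: 2000·(10·1000)² / (1000·1000·10·1990) = 10.05, p=0.0015. Smallest expected count: 10·1000/2000 = 5.0.
- 19 v 0: 206·(19·106)² / (100·106·19·187) = 22.19, p=2.5e-6. Smallest expected count: 19·100/206 = 9.2.

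**Logistic regression.** The maximum-likelihood odds ratio is a·(n2−c) / (c·(n1−a)). With c=0 it is infinite. Iterating the unadjusted fit:

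- 10 v 0: coefficient 6.6 with standard error 8.6 after 10 iterations, then 16.6 and 1271 after 20. Wald p goes from 0.44 to 0.99.
- 19 v 0: Wald p goes from 0.71 to 0.996 over the same iterations.

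The likelihood-ratio statistic from the same model stays finite: 13.91 and 29.52. For a single 2×2 table, Firth's penalty amounts to adding 0.5 to each cell: (10.5·1000.5)/(990.5·0.5) = 21.2 and (19.5·106.5)/(81.5·0.5) = 51.0.

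| Table | Min. expected | Chi-square p | Fisher p | Wald p | Likelihood-ratio p | Firth p |
|---|---|---|---|---|---|---|
| 10/1000 v 0/1000 | 5.0 | 0.0015 | 0.0019 | to 1 | 0.0002 | 0.0008 |
| B.1.351, 19/100 v 0/106 | 9.2 | 2.5e-6 | 4.1e-7 | to 1 | 5.5e-8 | 3.1e-7 |
| B.1.617.2, 5/100 v 1/106 | 2.9 | 0.084 | 0.110 | 0.12 | 0.072 | 0.097 |
| B.1.1.7, 2/100 v 0/106 | 0.97 | 0.143 | 0.234 | to 1 | 0.088 | 0.207 |

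Chi-square, Fisher, likelihood-ratio and Firth reach the same 5% decision in all four rows. Only Wald departs, in the first two.

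**How often an arm is empty.** At the forecast 10 per 1000 in both arms, exactly one arm has no cases in 41% of trials at 124 v 124 and in 29% at 124 v 1000. At assumed true rates of 10 v 1 per 1000, with 1000 per arm, the figure is 37%. Power there is 84% (chi-square), 75% (Fisher), 89% (likelihood ratio) and 42% (Wald, counting an empty arm as no rejection).

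**Group C at 124 against an enlarged Group A.** At 10 per 1000, C expects 124·0.01 = 1.24 cases. For 1/124 v 0/1000:

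- Chi-square: 1124·1000² / (124·1000·1·1123) = 8.07, p=0.0045, with a smallest expected count of 0.11.
- Fisher: the chance that a lone case falls in C, 124/1124 = 0.11.

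Exact type I error of chi-square, enumerated over binomial outcomes with equal true risks:

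- A=1000: at most 4.9% over risks of 0.05% to 2%.
- Risk 0.2%: 6.0% at A=800, 7.6% at A=600 and 9.1% at A=500.
- Fisher at A=500: below 3% over risks of 0.05% to 2%.

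The excess at A=500 comes mostly from one table. A lone case in C gives 624·500² / (124·500·1·623) = 4.04, just above 3.84, and at 0.2% its probability is 124·0.002·0.998^623 = 7.1%.

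**The case against.** A reader might infer that chi-square breaks down at the protocol's own counts. It does not. Expected counts reach 5.0 and 9.2 in the two decisive tables. Where they fall below 5, chi-square and Fisher are both non-significant. The exact size of chi-square is about 5.3% or less at 1000 per arm (common rates of 0.5% and 1%) and at the interim group sizes (6/206 and 2/206).

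A reader might also infer that only exact or penalised methods will do. Neither section 11.3.5 nor the Synopsis prescribes Wald, and the likelihood-ratio test of the planned model restores agreement. That objection stands. The likelihood-ratio test alone still gives no finite odds ratio, and it runs somewhat high (5.3% to 7.4% in the same settings).

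The comparison of 124 with an enlarged Group A is not clearly planned. Section 1.3 directs the further recruitment to heterologous v homologous Comirnaty, and section 11.3.5 puts the main analysis between the two randomised arms. If only randomised participants are used, 124 v about 124, chi-square is conservative (2.1% at a risk of 1%). With A at 1000 its total error stays within 5%. The fact that nearly all of that error favours A is a weak complaint, because Fisher is lopsided too (up to 3.0% in the same direction).

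A small-cell rule is often left to the SAP, which is not at hand, and contingency table analysis does not exclude an exact test. What remains is that the protocol positively names an adjusted model that fails on counts it prints. Section 11.1 presents 10 v 0 as extreme and the breakthrough analysis as underpowered, but few events make empty arms more likely.

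**Conclusion.** The point holds for the adjusted model. On 19/100 v 0/106 and on 10 v 0 per 1000, ordinary logistic regression gives no finite arm odds ratio. A Wald p-value near 1 then stands against chi-square p-values of 2.5e-6 and 0.0015, with no statement of which decides. For chi-square the point holds only conditionally: sparse breakthrough counts, Group C at 124, and an enlarged Group A. The inflation reaches about 9% if A stops near 500 at a true risk of 0.2%, and disappears at 1000.

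Assumptions: the section 1.3 counts reflect the binary cut-off (the text also speaks of very low titres); the interim denominators are 100 and 106; and the group of 106, which section 1.3 labels with prime and boost reversed, is Group A. The 1 per 1000 and 0.2% risks are illustrations, not protocol figures.

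The closing of Group C is not put in doubt. On the assumed B.1.351 table, chi-square, Fisher, likelihood-ratio and Firth p-values are all far below the 0.001 boundary in section 11.3.3.

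**What to change.** In section 11.3.5, and to match in the Synopsis:

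- Fit the site- and sex-adjusted model by Firth-penalised (or exact) logistic regression, with profile-likelihood or likelihood-ratio p-values and 95% confidence intervals, not Wald.
- When any expected cell count is below 5, replace chi-square by Fisher's exact or mid-p test with an exact 95% confidence interval.
- State which of the two results governs. This is still needed after the change: for 1/124 v 0/1000, Firth gives p=0.034 and Fisher 0.11.

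The cost is one or two sentences and a few lines of code. P-values in sparse tables become somewhat larger (for 5 v 1, 0.110 with Fisher instead of 0.084). No 5% decision changes in any table that the protocol reports or forecasts.

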### **Comparability of treatment arms**

The two randomized and the third non-randomized vaccination arms will be assessed descriptively for comparability of demographic and baseline characteristics. Administered study vaccine, medical history, disease duration, use of prior treatments and concomitant medications will be summarised by treatment arm using descriptive statistics.

### **T Cell analysis (pre-defined subgroup analysis)**

Efficacy analyses are performed for the comparison of Quantiferon results by treatment arm.

### **Safety Analysis**

Safety evaluations will be based on the incidence, type, severity and consequences (e.g. study discontinuation) of an adverse event (AE) as well as on clinically significant changes in the patient's physical examination, vital signs, and clinical laboratory results (including immunotoxicity). Statistical analysis includes tabulation per treatment group using descriptive measures which are absolute and relative frequencies for categorical data and means, standard deviations, medians and interquartile ranges for continuous data. All safety analyses will be performed on the safety population.

All analyses will be performed in SPSS 26.0 or StataMP 16.0.

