|                                           | 
 
6. Subjects with previous positive PCR-test result for SARS-CoV-2 or positive anti-SARS-CoV-2 N protein antibody test
 
7. History of leukemia, lymphoma, or underlying bone marrow disorder (eg, myelodysplasia, myeloma, myeloproliferative disorder) or history of bone marrow transplant.
 
8. Malignancy that required treatment with chemotherapy, immunotherapy, radiation therapy, or other antineoplastic target therapies within 24 months prior to study enrollment.
 
9. Has participated in an interventional clinical study within 30 days prior to study inclusion
 
 
Subjects are excluded from the third dose of vaccination if any of the following criteria apply in addition to the above mentioned ones:
 
 
1. Participant already received a third dose of vaccination.
 
2. Subjects with positive PCR-test result for SARS-CoV-2 after study enrolment or a positive anti-SARS-CoV-2 N antibody test on day 180.
 
 |
| Methodology of the study           | 
Prospective controlled randomized study on vaccination against SARS-CoV-2; after an interim analysis the study is continued as a non-randomized study. Participants that have already been enrolled will be followed until day 180. New participants are only enrolled into Group A and Group B.
 
Dosage BNT162b2: 30µg/0.3ml/injection
 
Dosage ChAdOx1-S: 5x10^10 viral particles /0.5ml/ injection
 
The study includes 3 arms:
 
Group A (randomized): ChAdOx1-S prime and BNT162b2 boost 12 weeks (± 1 week) between prime and boost. Until the interim analysis this group had been randomized. Following interim analysis new participants will be enrolled in a non-randomized, non-blinded fashion.
 
Group B (non-randomized): 2 Doses of BNT162b2, 4 - 6 weeks between prime and boost
 
Group C (randomized): 2 Doses of ChAdOx1-S, 12 weeks (± 1 week) between prime and boost. Recruitment of new participants is discontinued for this group after interim analysis.
                                       |

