If patient discontinues study participation for reasons unrelated to an adverse event, immunization of the patient will be continued according to the recommendations of the Austrian NIG (Nationales Impfgremium). No additional patient will be enrolled to replace that subject.

Reasons for removal investigational treatment or observation might include:

- Withdrawal of consent
- Administrative decision by the investigator
- Pregnancy
- Significant protocol deviation
- Subject noncompliance
- Serious Adverse event
- Other safety concern of the investigator or sponsor
- Death
- Lost to follow-up (participant repeatedly fails to return for scheduled visits without stating an intention to withdraw consent & he/she cannot be contacted by the study site after 3 contact attempts-these contact attempts must be documented in the participant`s medical record)

Participants that had been recruited during the first part of the study when this has still been conducted as a blinded and randomized study might request premature unblinding. In that case, participants might be kept part of the study after unblinding and will be further followed regarding durability of immune responses and breakthrough infections until day 180. If eligible, these participants might be included in a third vaccination.

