## 5.5 Visit II, IV - VIII (Day 1, 3 – 7 after boost shot)

Subjects have to report information on reactogenicity on Day 1 and between Day 3 and Day 7 after boost shot. This information will be reported using an eDiary or via telephone call. The following information will be collected:

- pain at injection site
- erythema (redness) at injection site
- swelling/induration (hardness) at injection site
- localized axillary swelling or tenderness ipsilateral to the injection arm
- Headache
- Fatigue
- myalgia (muscle aches all over the body)
- arthralgia (aching in several joints)
- nausea/vomiting
- body temperature (potentially fever)
- chills
- other AEs

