## 6.8 Blinding and Unblinding

All groups have already received the prime vaccination. The two groups that have received a prime with Vaxzevria (ChAdOx1-S) will be randomized into a group that receive again Vaxzevria (ChAdOx1-S) or Comirnaty (BNT162b2). The administration is blinded. The participants only are not informed in which arm they were randomized.

The syringes with the vaccines will be prepared in a separate room and brought into the vaccination room immediately before application. The unblinding will take place on day 90 post boost.

All participants recruited after closing of the homologous Vaxzevria arm that have received the prime immunization with Vaxzevria will receive the boost vaccination with Comirnaty in a non-blinded fashion.

All participants who have already received a prime with Comirnaty (BNT162b2) will receive Comirnaty (BNT162b2) again.

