#### Safety population

The safety population will include all patients who received at least one boost vaccination. In the safety analyses, patients will be analysed by vaccine received, regardless of any errors of dosing or vaccine administration.

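### The per-group safety table was not adapted to the change of design: Group A pools a randomised, participant-blinded cohort with a later open-label one, so a descriptive reactogenicity comparison with Group C is neither randomised nor under equal blinding

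*Protocol*

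**What the plan says.** Section 11.3.2 of the protocol defines the population: "The safety population will include all patients who received at least one boost vaccination". It makes no distinction by recruitment phase. Section 11.3.5, Safety Analysis, then says: "Statistical analysis includes tabulation per treatment group using descriptive measures". It adds that every safety analysis uses that population.

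The groups were recruited under different conditions:

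- **Group A.** It was randomised up to the interim analysis. For the period after it, the Synopsis says: "Following interim analysis new participants will be enrolled in a non-randomized, non-blinded fashion".
- **Group C.** It was recruited only in the randomised phase: "Recruitment of new participants is discontinued for this group after interim analysis".
- **Group B.** It was never randomised. Under section 6.8 a Comirnaty prime is always followed by a Comirnaty boost, so these participants know what they receive.

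On blinding in the randomised phase, section 6.8 says: "The participants only are not informed in which arm they were randomized". On its end: "The unblinding will take place on day 90 post boost".

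Section 5.5 collects pain, headache, fatigue, myalgia, chills and similar symptoms on Day 1 and Days 3 to 7 after the boost. On how: "This information will be reported using an eDiary or via telephone call".

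**The concern.** First-week symptoms are what participants say they felt, and such reports can depend on knowing which vaccine was given. Under the stated layout the Group A column mixes people who did not know with people who did. The Group C column beside it contains only people who, by design, did not know, and the Group B column only people who did.

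Blinding is not the only thing lost. The later Group A participants were not randomised and joined in a later period, so they may differ from Group C in other ways too.

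A secondary objective is detailed safety and tolerability after the second dose, with emphasis on the heterologous arm. The column that mixes the two conditions is therefore the one of most interest. The trial does have a randomised, participant-blinded contrast of A with C for tolerability, but the safety section does not ask for it to be tabulated.

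**Working it through.** **Inputs from the protocol**

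- Group C: 124 randomised; Groups A and B: up to 1000 each (Synopsis, planned number of subjects).
- Allocation of A to C: 1:1 (section 11.2).
- Heterologous participants analysed at Day 30 for the interim: 106 (section 1.3, which names the prime and boost in reverse order).

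**The plan's own figure.** 124 + 1000 + 1000 = 2124, which matches the stated total. The protocol gives no figure for the safety comparison itself.

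**Size of the blinded part of Group A.** It is not stated. The 1:1 allocation suggests about 124. The interim count gives 106, which covers only those who had reached Day 30. I use 106 to 124.

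**Open-label share of the Group A column**, w = 1 − n_blinded / n_A:

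| Final size of Group A | 124 blinded | 106 blinded |
|---|---|---|
| 1000 | 1 − 124/1000 = 87.6% | 1 − 106/1000 = 89.4% |
| 500 | 1 − 124/500 = 75.2% | 1 − 106/500 = 78.8% |
| 300 | 1 − 124/300 = 58.7% | 1 − 106/300 = 64.7% |

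The share in Group C is 0% by design. The 88% to 89% is a ceiling, because 1000 is the maximum for Group A.

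**Illustration only.** Suppose knowing the vaccine shifts the reported rate of a symptom by d percentage points and the true rates in A and C are equal. The pooled difference A − C is then w × d. The values of d are assumptions; nothing in the protocol supports a particular size or sign.

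- d = 5, Group A at 1000: 0.876 × 5 = 4.4 to 0.894 × 5 = 4.5 points.
- d = 10, Group A at 1000: 0.876 × 10 = 8.8 to 0.894 × 10 = 8.9 points.
- Group A at 300 to 500: 0.587 × 5 = 2.9 to 0.788 × 5 = 3.9 points for d = 5, and 5.9 to 7.9 points for d = 10.

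With Group A restricted to its randomised participants, w = 0 by design and this term disappears.

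**Precision given up**, at an assumed symptom rate of 50%, with SE = √(0.25/124 + 0.25/n_A):

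- Pooled A, n_A = 1000: √(0.25/124 + 0.25/1000) = 4.8 points.
- Randomised A, n_A = 124: √(0.25/124 + 0.25/124) = 6.4 points (6.35 unrounded).
- Randomised A, n_A = 106: √(0.25/124 + 0.25/106) = 6.6 points.

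The 95% half-width (1.96 × SE) goes from 9.3 points to 12.4–13.0 points. The rise is modest because the 124 in Group C already limit precision.

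**The case against.** The strongest objection is that table layout belongs in the statistical analysis plan, which is not at hand. The sentence in 11.3.5 says what the analysis includes, so it does not forbid a split. That much is true, and a reader should not conclude that the protocol rules out separate tabulation. But the protocol does fix the population and the grouping. Sections 6.8 and 11.3.1 were updated for the open-label phase and the safety text was not. The comparability paragraph in 11.3.5 still describes two randomised arms and one non-randomised arm, although most of Group A may not be randomised. Someone following the text as written would pool.

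Second, the table is descriptive. No test or error rate is affected, and no formal A-versus-C estimate of harm is planned. This stands and limits the weight of the point. Even so, descriptive tables are the stated form of the safety analysis, and readers will compare columns.

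Third, the interim analysis covered safety at Day 30 in 100 homologous and 106 heterologous Vaxzevria-primed participants, which is roughly the randomised cohort. It would therefore be wrong to infer that the blinded comparison has never been made. What is missing is a provision to report it in the final safety analysis.

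Three further inferences go too far:

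- **That section 1.4 already reflects the mixed column.** Its statement that side effects are similar concerns participants already recruited, before open-label enrolment into Group A.
- **That Group C is blinded without exception.** Section 4.4 says that participants from the "blinded and randomized study might request premature unblinding". This is unlikely to matter much by Day 7, but participant-blinded by design to Day 90 is the accurate description.
- **That every safety outcome is affected alike.** Laboratory values are much less exposed to reporting behaviour.

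**Conclusion.** The point holds as a risk of bias in how safety will be displayed. As written, the Group A column combines about 106 to 124 randomised, participant-blinded participants with later open-label ones. The open-label share is up to about 88% to 89% if Group A reaches 1000, and about 59% to 79% if it ends between 300 and 500. Comparing that column with Group C for self-reported symptoms in the first week is neither randomised nor under equal blinding.

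The shares rest on an inferred count of blinded Group A participants. The shifts in percentage points rest on assumed reporting effects and serve only to show scale. A reader might infer that observed differences between the groups will in fact be caused by knowledge of the vaccine. The documents do not support that: they give no size and no direction for such an effect. The text should be corrected because the remedy is cheap and uses data already being collected.

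**What to change.** In section 11.3.5, Safety Analysis:

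1. Tabulate reactogenicity and other subjective adverse events for Group A in two columns: the randomised, participant-blinded cohort and the non-randomised, open-label cohort. State the number in each.
2. Base any comparison with Group C on randomised Group A only.
3. Show open-label Group A beside Group B and label that comparison as non-randomised. Matching on blinding does not remove the differences in prime vaccine and interval.
4. Keep a pooled Group A column for serious adverse events and adverse events of special interest, where numbers matter more than reporting behaviour.

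The safety population in 11.3.2 can stay as it is. The cost is one extra column and a few sentences, with no new data. The price is the wider interval for A versus C shown above.
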